## Abstract

**Background:**

The double-lumen tube (DLT) is an essential equipment for thoracic anesthesia and the precise position of DLT placement is particularly important for anesthesia and surgery. However, the incidence of DLT malposition remains high and it leads to lung isolation failure and hypoxemia during one-lung ventilation. This trial aims to explore the clinical application and efficacy of intubation in the lateral position under general anesthesia induction to reduce the incidence of DLT malposition in patients undergoing unilateral video-assisted thoracic surgery (VATS).

**Methods:**

In this prospective, single-center, parallel group, randomized, controlled trial, we will recruit 108 patients, aged 18–80 years, scheduled for elective unilateral VATS with DLT intubation under general anesthesia, and they will be randomly assigned to two groups: a lateral DLT intubation group (group L) and a conventional supine DLT intubation group (group C). The left-sided DLT will be used to intubate in patients of both groups. The position of DLT will be confirmed and adjusted by using the fiberoptic bronchoscopy (FOB). The primary outcome is the incidence of DLT malposition observed via the FOB, and the secondary outcomes include the time of intubation, the frequency and duration of re-adjustments of DLT placement under FOB, whether to re-intubate, intraoperative vital signs, and postoperative recovery.

**Discussion:**

Accurate DLT positioning is crucially important for thoracic surgery, but the incidence of DLT malposition is still high in the present clinical practice of thoracic anesthesia. This trial aims to investigate whether lateral DLT intubation can reduce the incidence of DLT malposition, with more stable intraoperative vital signs and less postoperative complications.

**Trial registration:**

The study protocol was registered at Chinese Clinical Trial Registry (http://www.chictr.org.cn) with registration number: ChiCTR2200060794 on June 11, 2022.

**Supplementary Information:**

The online version contains supplementary material available at 10.1186/s13063-023-07075-9.

## Introduction

### Background and rationale {6a}

The thoracic surgery has drastically increased in recent years, especially in the light of the outbreak of coronavirus diseases 2019. Routine “passive” computed tomography of the chest screening of inpatients timely detects some pulmonary disease requiring thoracic surgeries. With the advantages of less damage, minimizing complications, and quick postoperative recovery, the video-assisted thoracic surgery (VATS) has been the standard approach of treatment in most thoracic surgery [1]. The double-lumen tube (DLT) intubation can achieve lung isolation and one-lung ventilation (OLV) which are the basis of modern thoracic anesthesia and surgery [2, 3]. The accurate position of DLT placement can effectively isolate the ventilation pathways of both lungs to ventilate separately at the bronchial level, resulting in full atrophy of the operated lung and good exposure of the operative field to facilitate surgical operations, also preventing pus, bronchial secretions, or blood from the operated lung entering the healthy lung [2]. However, many reasons lead to DLT malposition which deviates from the accurate position, generally including neck flexion or extension during shifting the patient from supine to lateral position, surgical manipulation, and coughing [4–8]. Related to differences in DLT types, intubation methods, or definitions of malposition, the incidence of DLT malposition mainly varied in 26–37% [9–11], and about 40% of DLT-related complications are due to DLT malposition, including poor lung isolation, hypoxemia during OLV, atelectasis, and severely impaired ventilation, which can cause hypoxia, gas trapping, atelectasis, tension pneumothorax, cross-contamination and infections, and interference with surgical procedures [9, 12, 13]; thus, the accurate position of DLT placement plays a crucially important role in thoracic anesthesia. Knowing how to both properly position a DLT and correct a malpositioned DLT is significant for airway management during thoracic surgery and in other cases where single-lung isolation is necessary. The fiberoptic bronchoscopy (FOB) is the most effective and reliable method to confirm and adjust the DLT position, and after assessing with FOB, studies have revealed that DLT becomes malpositioned in 25 to 54% of cases, requiring prompt repositioning [3, 14–17]. Even if initial DLT placement is performed successfully, DLT malpositioning commonly occurs, as blind intubation and lateral positioning of the patient can often displace the DLT.

Passive neck flexion or extension movement of patients from supine to lateral position after DLT intubation are likely to lead to DLT malposition, and a recent study reported that shifting patients to lateral position increased endobronchial cuff pressure due to changes in gravity and the curvature or length of the left main bronchus [18]. Thus, we hypothesize it will be possible to assist patients undergoing VATS in the surgically required lateral position before induction of anesthesia, and then to carry out DLT intubation under general anesthesia induction, which can directly avoid the possible adverse effects of lateral positioning. After reviewing related articles, less references of lateral DLT intubation can be found. Martinez et al. [19] mentioned in their article that an important and unique issue for non-intubated thoracic surgery (NIVATS) was the training of lateral position intubation for emergencies, as patients in NIVATS were likely to require to DLT intubation, and lateral intubation was not difficult according to their experiences. In addition, Ajimi et al. [20] reported a case of successful left-sided DLT intubation in the right lateral position for a patient with a giant mediastinal tumor with tracheal compression, and OLV was performed safely during thoracic surgery without ventilatory failure or hypoxemia. Therefore, we design this trial to explore the clinical application and efficacy of intubation in the lateral position under general anesthesia induction, and indicate it can reduce the incidence of DLT malposition in patients undergoing unilateral VATS.

### Objectives {7}

We will conduct a prospective, single-center, parallel group, randomized, controlled trial to explore the effect of intubation in the lateral position under general anesthesia induction on the position of DLT placement in patients undergoing unilateral VATS. We will study whether the DLT intubation in the lateral position under general anesthesia induction can reduce the incidence of DLT malposition with more stable intraoperative vital signs and fewer postoperative complications, compared with the conventional supine DLT intubation.

### Trial design {8}

This study will be conducted as a prospective, single-center, parallel group, randomized, controlled trial.

## Methods: participants, interventions, and outcomes

### Study setting {9}

The study will be conducted in patients undergoing elective unilateral VATS with DLT intubation in Huzhou Central Hospital, Zhejiang, China.

### Eligibility criteria {10}

The inclusion and exclusion criteria for participants in this study are as follows:

Inclusion criteria:Scheduled to undergo the unilateral VATS with left-sided DLT intubation under general anesthesiaAmerican Society of Anesthesiologists (ASA) score of I to IIIAge 18–80 years with capacityAgree to participate in this study and sign informed consent

Exclusion criteria:Difficulty in intubation at preoperative assessment (body mass index > 30 kg/m^2^, limited neck movement, mouth opening < 3 cm or Mallampati III–IV grades)Failure of multiple attempts to DLT intubateSevere mental illness and communication difficultiesRefusal to sign informed consentHistory of pulmonary surgery

### Who will take informed consent? {26a}

Appropriate participants will be jointly identified by the chief physician of anesthesia and cardiothoracic surgery at our hospital. We will give the participants sufficient time to consider and voluntarily choose to participate in the study, then will obtain the written informed consent on the day before surgery from each participant of study.

### Additional consent provisions for collection and use of participant data and biological specimens {26b}

Before obtaining the participants' informed consent, we will explain the implement methods of lateral and supine DLT intubation, and account for the preoperative, intraoperative, and postoperative data needing to be collected. The specific content of methods and data will also be listed in the informed consent form. This study will not involve the collection of biological specimens.

### Interventions

#### Explanation for the choice of comparators {6b}

With the special position requirement of thoracic surgery, the patients often need to be shifted to the left or right lateral position after anesthesia and intubation. In thoracic anesthesia, the patients are placed conventionally in the supine position for induction and intubation, then be moved to the lateral position after completing the DLT positioning. Therefore, we chose the supine DLT intubation as the control.

### Intervention description {11a}

#### Preparing

All participants are routinely fasted for 8 h before surgery and routinely monitored with a 5-lead electrocardiogram, non-invasive blood pressure or invasive arterial blood pressure, and oxygen saturation in the operation room.

#### Description for intervention

Both groups will be induction and maintenance with total intravenous anesthesia, followed by the left-sided DLT (Broncho-Cath®, Mallinckrodt Medical Ltd., Hampshire, Ireland) intubation to mechanical assisted ventilation. Lateral DLT intubation group (group L): investigators assist the participant to a comfortable and surgically required lateral position before induction and intubate DLT with a video laryngoscope after induction, then confirm and adjust the DLT position using the FOB to complete the positioning of DLT. Conventional supine DLT intubation group (group C): investigators intubate DLT with a video laryngoscope after induction in the conventional supine position, then confirm and adjust the DLT position using the FOB to complete the positioning of DLT, and use the FOB again to confirm the DLT position after lateral positioning.

#### Introduction for investigators

This study will be completed with the joint participation of the Department of Anesthesiology, the Department of Cardiothoracic Surgery and the Department of Operating Room Nursing. For anesthesia, the investigator has extensive experience in thoracic anesthesia and has specially trained in lateral intubation.

#### Criteria for discontinuing or modifying allocated interventions {11b}

The investigator will terminate the experiment for this participant if one of the following occurs during the experiment:Participants in the operating room not accept the intervention after learning about their groupingAttempting DLT intubation in lateral position ≥ 3 times or intubation time ≥ 3 minSwitch to supine DLT intubation after unsuccessful attempts to lateral intubationPostoperative follow-up could not be completed due to various reasons

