#### Sample size {14}

This trial focuses on whether intubation in the lateral position under general anesthesia will reduce the DLT malposition rate observed via the FOB in patients proposed for unilateral VATS; therefore, the expected sample size is calculated based on the current DLT malposition rate. According to previous studies, the incidence of DLT malposition is about 30% [9]. Expecting a 50% reduction in malposition rate to be considered an effective intervention, we chose *α* = 0.05 and test efficacy *β* = 80%, which is calculated to yield 48 cases in each group by using the PASS 15.0 software. Considering a 10% drop-out rate, the final sample size is derived as at least 54 cases per group, with a total of 108 patients included.

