### Assignment of interventions: allocation

#### Sequence generation {16a}

The computerized random number generator is used to generate random sequences on a 1:1 basis, and the random sequence will be put into a sealed, opaque and sequentially numbered envelope by the investigator. When the participant is admitted to the operating room the investigator will open the envelope to obtain a random sequence to determine the grouping. Participants with random sequences 1–54 are assigned to group L, while 55–108 are assigned to group C. Each participant will be given a unique study sequential number on the envelope cover in the order of their participation in this study. The random sequences of all participants and its corresponding study sequential numbers will be recorded in the randomization list.

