### Statistical methods

#### Statistical methods for primary and secondary outcomes {20a}

The SPSS statistical software version 26.0 (IBM) will be used for statistical analysis. Primary and secondary outcomes will be analyzed as follows: use Kolmogorov–Smirnov test to determine whether continuous data follows normal distribution. Continuous data following a normal distribution are expressed as mean ± standard deviation (‾x ± s), while nonnormal distributions are expressed as median (quartile spacing). The independent samples *t* test will be used for comparison between groups of normally distributed continuous data. The Mann–Whitney *U* test will be used for comparison of non-normally distributed continuous data. Count data are expressed as number of cases (rate) and tested by chi-square test or Fisher’s exact test. If subsequent multi-factor analysis will be required, multiple linear regression or logistic regression models are selected according to continuous-type or sub-type dependent variables. The data analysis of this study adopts the principle of intentional analysis. Multiple interpolation will be used for the analysis of missing data, and sensitivity analysis will be performed. Probability values < 0.05 will be considered significant.

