#### Methods in analysis to handle protocol non-adherence and any statistical methods to handle missing data {20c}

Given that we will explain the intervention in detail and emphasize cooperation matters to the patient during pre-anesthesia evaluation and obtaining informed consent, we guess that few patients will protocol non-adherence. If needed, multiple interpolation will be used for the analysis of missing data, and sensitivity analysis will be performed.

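### Participants are terminated or excluded after randomisation for failed intubation, partly under rules that only group L can meet, which conflicts with the declared intention-to-treat principle

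*Protocol article*

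**What the plan says.** All places are in the protocol article.

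- **Timing of allocation, {16a}:** "When the participant is admitted to the operating room the investigator will open the envelope". Positioning, induction and intubation follow ({11a}, {16c}).
- **Termination, {11b}:** "The investigator will terminate the experiment for this participant if one of the following occurs during the experiment". Four items follow: (1) refusal once the allocation is known; (2) three or more attempts in the lateral position, or an intubation time of 3 minutes or more; (3) a switch to supine after failed lateral attempts; (4) postoperative follow-up not completed.
- **Exclusion, {10}:** failure of multiple attempts at intubation is listed separately from predicted difficulty at preoperative assessment, and is not limited to one arm.
- **Analysis principle, {20a}:** "The data analysis of this study adopts the principle of intentional analysis". I read this as intention-to-treat.
- **Non-adherence and missing data, {20c}:** little non-adherence is expected; if needed, "multiple interpolation will be used for the analysis of missing data, and sensitivity analysis will be performed".
- **Outcomes, {12} and {18a}:** malposition is a tube displacement of more than 1.0 cm, observed by bronchoscopy in theatre. Intubation time runs from laryngoscope use to bronchoscopic confirmation. Re-intubation is a secondary outcome.

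**The concern.** Every {11b} event happens after randomisation, and most happen at or around intubation, the step being tested. Ending participation at that point removes people because of how the allocated technique went. Two of the four items are worded so that only group L can meet them. A failed or converted lateral intubation is itself a result of the trial, whose stated aim includes the clinical application of the technique.

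If these participants leave the data, the comparison is no longer between the groups as randomised. A favourable result for lateral intubation could then not be separated from selective loss of its failures.

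**Working it through.** **1. Which arm can meet each rule**

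| Rule | Group L | Group C |
|---|---|---|
| {11b} refusal after allocation | yes | yes |
| {11b} three or more lateral attempts | yes | no |
| {11b} 3 min limit (same item) | yes | unclear |
| {11b} switch to supine | yes | no |
| {11b} follow-up not completed | yes | yes |
| {10} failed multiple attempts | yes | yes |

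**2. Why imputation does not repair it.** If outcome collection stops at failure, no failed lateral intubation has an observed outcome. The imputation model can then learn group L outcomes only from successes, and nothing in the data can test whether failures resemble them.

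**3. Secondary outcomes.** Re-intubation through conversion would drop out of group L by rule. Intubation time would be cut off at 3 minutes if {11b} uses the {12} interval and the data are dropped. As an illustration, assume log-normal times (log SD 0.4) with the cut-off in group L only. Medians of 90, 120 and 150 s then remove about 4%, 16% and 32% of group L and lower its mean from 97 to 92 s, 130 to 112 s and 162 to 126 s. The documents give none of these inputs.

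**4. Primary outcome, no true effect**

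Inputs from the plan:
- control rate: "the incidence of DLT malposition is about 30" per cent ({14})
- significance level: "we chose *α* = 0.05" ({14}) and "Probability values < 0.05 will be considered significant" ({20a}); sidedness is not stated, so two-sided is assumed
- 54 per group: 48/(1 − 0.10) = 53.3, rounded up to 54, which reproduces the plan's drop-out step. The 48 itself does not reproduce (30% v 15% at 80% power needs 121 per group two-sided). That is a separate matter and nothing here depends on it.

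Assumed, because the documents do not give them: f, the share of group L removed, and r, the malposition risk of those removed.

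Observed group L rate = (0.30 − f × r)/(1 − f). For f = 0.10:
- r = 0.30: (0.30 − 0.03)/0.90 = 30.0%
- r = 0.50: (0.30 − 0.05)/0.90 = 27.8%
- r = 0.70: (0.30 − 0.07)/0.90 = 25.6%

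Type I error by simulation (200,000 trials per cell, 54 randomised per arm, removal from group L only, uncorrected two-proportion test):

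| f | r | Observed group L rate | Type I error | Part favouring lateral |
|---|---|---|---|---|
| 0.10 | 0.30 | 30.0% | 0.052 | 0.026 |
| 0.10 | 0.50 | 27.8% | 0.058 | 0.044 |
| 0.10 | 0.70 | 25.6% | 0.079 | 0.072 |
| 0.20 | 0.50 | 25.0% | 0.084 | 0.078 |
| 0.20 | 0.70 | 20.0% | 0.201 | 0.200 |

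**5. Primary outcome, planned effect.** The plan states: "Expecting a 50% reduction in malposition rate to be considered an effective intervention". That means 15% in group L. Suppose a converted patient carries the control risk of 30% and the others 15%. With 10% converting, the as-randomised rate is 0.90 × 0.15 + 0.10 × 0.30 = 16.5%. With 20% it is 0.80 × 0.15 + 0.20 × 0.30 = 18.0%. Dropping the converted patients would report 15% in both cases. The conversion shares are assumed.

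**The case against.** **Termination need not mean deletion.** The {11b} list stands under a heading about discontinuing or modifying interventions, and it does not say that data are discarded. This is fair: a reader might infer that terminated participants have no outcome, and the text does not say so. But it speaks of ending the experiment for the participant, describes no continued outcome collection, and {10} makes failure an exclusion. The sections still conflict.

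**Group C loses people too.** A reader might infer that group C keeps everyone while group L keeps only easy cases. The documents do not support that. Refusal, incomplete follow-up and the {10} exclusion can occur in either arm, and the reach of the 3-minute limit is unclear. Only the attempt count and the conversion item belong clearly to group L.

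**Bias in the malposition rate is not established.** It requires removed patients to be at higher risk than retained ones. A converted patient would presumably be turned afterwards, as in group C. At a 30% risk the null case shows no distortion, and no passage supports a risk of 50% or more. This objection stands against any claim of certain bias. It does not exclude bias if lateral intubation works as planned, as step 5 shows.

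**The {10} exclusion may refer to past failed intubation,** since eligibility is checked the day before surgery. That is possible but the weaker reading. For the study intubation, failure can be known only after randomisation.

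**Conclusion.** The concern holds as a contradiction between stated rules. Sections {10} and {11b}, followed as written, remove randomised participants for failure of the technique, while {20a} declares analysis by intention. Imputation does not resolve this.

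The direction is clear for re-intubation, where group L would lose its worst results. It is conditional for intubation time, on the 3-minute limit using the {12} definition. For the malposition rate, bias toward group L is possible and depends on two quantities the documents do not give. With 10% of group L removed the effect on type I error is modest: about 5%, 6% or 8% at risks of 30%, 50% or 70%.

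A reader might infer far larger distortion. A type I error near 55% does arise with 20% removed, but only if every one of them is malpositioned. That is an extreme bound, and its removal share is double the 10% drop-out in {14}.

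**What to change.** Reconcile {10}, {11b} and {20a}, leaving the attempt, time and conversion limits as they are:

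1. State that meeting an {11b} criterion does not end outcome collection, subject to the participant's consent, and that all randomised participants are analysed in their allocated group.
2. Remove post-randomisation intubation failure from the exclusions in {10}.
3. Remove incomplete 24 h follow-up from the {11b} list, since the primary outcome is already observed in theatre.
4. Record failed or converted intubation as an outcome under re-intubation, and run intubation time through any conversion to the final bronchoscopic confirmation.
5. Assess malposition in converted patients by the {12} definition. Do not count conversion itself as malposition: that departs from the definition and, because only group L can convert, would penalise that arm.
6. In sensitivity analysis, vary the assumed outcome only where it is truly missing.

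The cost is a short amendment with ethics committee approval. No extra visits are needed, because the patients are still in theatre and then on the ward. The downside is that the apparent benefit of lateral intubation may be smaller.

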#### Relevant concomitant care permitted or prohibited during the trial {11d}

All study participants will receive standard postoperative care in the operating room, the postanesthesia care unit (PACU), the intensive care unit (ICU), or the ward.

